### Allocation

For randomization, the “blockrand” function in R 4.1.0 (Ross Ihaka, Robert Gentlemen, New Zealand) will be employed to generate random sequences. We will first divide the seven communities into the compulsory randomization cluster (three communities) and patient preference cluster (four communities) via cluster randomization. Then, we will generate a random sequence with a block size of four to randomly assign the patients into the HSM or control group in a 1:1 ratio in a compulsory or voluntary manner.

The random sequence will be concealed using scratch cards printed with a random number corresponding to the participation order. Until the coating is scratched, neither the patients nor the investigators will have knowledge about the group assignments. An independent investigator who is not involved in the implementation and follow-up of this study will generate and save the randomization sequence and prepare scratch cards. Although blinding is impossible for the patients and physicians, the data analysts will not be aware of the treatment allocation.

Patients who have a clear preference may be free to choose to enter the HSM or control group, with an allocation ratio of 1:1. Hence, when either nonrandomized group is full, the remaining patients will have to enter another nonrandomized group.

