### Data collection and management

At each study site (i.e., community healthcare center), a community physician will be responsible for patient recruitment, HSM training, and outcome assessment; a clinical coordinator will be responsible for regular contact with patients with regard to follow-up visits, recording basic information, and distributing moxibustion materials. Prior to the start of the trial, all investigators will be trained on the standard operating procedure and complete simulated baseline and follow-up visits before being allowed to conduct the investigation.

Raw data will be recorded on paper-based case report forms stored in a lockbox at each study site. Electronic data entry will be performed at any interim analysis and at the end of follow-up by an approach in which two clinical coordinators independently and repeatedly enter the data into standardized forms created in Microsoft Access (Microsoft Corporation, USA). The electronic data set will be anonymized and kept confidential. Only the blinded data analyst can access the data set.

The following trial committees will be established for quality assurance: a steering committee consisting of acupuncturists, cardiologists, methodologists, and statisticians and responsible for study design, maintenance of the quality of study conduct, safety monitoring, and study publication; a coordinating center consisting of the principal coordinating investigator and the coordinating investigators of each community and responsible for the overall study conduct, interactions with the communities and sponsors, and reporting trial advancements to the steering committee; an independent endpoint adjudication committee consisting of cardiologists and acupuncturists and responsible for reviewing the assessment of the primary endpoint and subjective outcomes; and an independent data-monitoring committee consisting of acupuncturists, cardiologists, methodologists, and statisticians for monitoring the data management, directing the interim analysis, and deciding whether to continue the trial based on the results of safety, efficacy, and compliance assessment.

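### A single fixed block size of four in an open-label trial leaves allocation partly predictable to the recruiting physician: about 2–4% of allocations certain under one reading, up to one third under another

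*Protocol article*

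**What the plan says.** All references are to the protocol article.

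- **Block size and ratio (Allocation).** "we will generate a random sequence with a block size of four to randomly assign the patients". Allocation to the two arms is equal, for compulsory and voluntary randomisation alike. One size is given, with no mention of varying it.
- **Role of the communities (Allocation).** "We will first divide the seven communities into the compulsory randomization cluster (three communities) and patient preference cluster (four communities) via cluster randomization". The section does not say whether patient-level sequences or card series are then separate for each community.
- **Concealment (Allocation).** "The random sequence will be concealed using scratch cards printed with a random number corresponding to the participation order". It adds: "Until the coating is scratched, neither the patients nor the investigators will have knowledge about the group assignments". The sequence holder is independent: "An independent investigator who is not involved in the implementation and follow-up of this study will generate and save the randomization sequence".
- **Blinding (Allocation).** "Although blinding is impossible for the patients and physicians, the data analysts will not be aware of the treatment allocation".
- **Who recruits (Data collection and management).** At each site, "a community physician will be responsible for patient recruitment, HSM training, and outcome assessment".
- **Numbers (Sample size estimation).** 120 patients in compulsory randomisation and 40 in voluntary randomisation, so 160 randomised in all.

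**The concern.** Concealment has two parts. The next card must be unreadable, and its content must not be deducible from the cards already opened. The scratch coating and the independent sequence holder deal with the first. A fixed block of four weakens the second: once two patients in a block have gone to the same arm, the rest of that block is known.

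Here the person who invites patients also learns their assignments, because that physician trains those allocated to HSM and follows both arms. A recruiter who can foresee the next arm, even imperfectly, can defer or bring forward patients according to blood pressure, motivation or likely compliance. That would affect the randomised SBP comparison, and keeping the analysts unaware of allocation cannot undo it.

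**Working it through.** The article gives no figure for predictability, so there is none to reproduce on this point. Its sample-size figure does reproduce (40.19 / 0.80 = 50.2, so 51 per arm) and is unaffected.

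**Inputs from the article:** block of four, 1:1, so six equally likely sequences and 6 × 4 = 24 allocations; three compulsory and four preference communities; 120 and 40 randomised patients; one physician per site.

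**Assumptions:** the observer knows the block size and the card's position in the block. In the shared-sequence case, S sites recruit at equal rates in random order, so a physician sees any given earlier allocation with probability q = 1/S.

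**Step 1. Allocations known with certainty.** An allocation is certain once two earlier ones in the block have been seen in the same arm.
- Third position: the first two agree (probability 1/3) and both were seen (1/S²), giving 1/(3S²).
- Fourth position: exactly two of the first three share an arm, and both must have been seen, giving 1/S².
- Average over four positions: (1/(3S²) + 1/S²) / 4 = 1/(3S²).

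With the whole sequence in view (S = 1) this is 8/24 = 1/3.

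**Step 2. Best-guess success by position.**
- First: 1/2.
- Second: 1/2 + q/6.
- Third: 1/2 + [1 − (1 − q)²]/6.
- Fourth: 1/2 + [1 − (1 − q)³]/6 + q³/3.

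For q = 1 the mean is (1/2 + 2/3 + 2/3 + 1)/4 = 17/24 = 70.8%. For q = 1/3 it is (0.500 + 0.556 + 0.593 + 0.630)/4 = 56.9%. For q = 1/4 it is (0.500 + 0.542 + 0.573 + 0.602)/4 = 55.4%.

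| Reading | Certain | Best guess right |
|---|---|---|
| Series per community, or assignments pooled | 1/3 = 33.3% | 70.8% |
| Shared across 3 sites, own site seen | 1/27 = 3.7% | 56.9% |
| Shared across 4 sites, own site seen | 1/48 = 2.1% | 55.4% |

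In patients, the first row is 120/3 = 40 compulsory and 160/3 = 53 in total. The shared readings give 120/27 = 4.4 compulsory and 40/48 = 0.8 voluntary. One sequence across all seven sites would give 1/147 = 0.7%.

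**Step 3. Illustration in mmHg.** Suppose a recruiter always acts on the best guess, and patients steered to the two arms differ in prognosis by +η and −η. With p the success rate, the between-arm bias is 2η(2p − 1): 0.83η with the full view, and 0.28η or 0.22η with a shared sequence over three or four sites. For η of 1 to 3 mmHg (an assumption with no support in the article), that is 0.8 to 2.5 mmHg or about 0.2 to 0.8 mmHg, against the planned 5 mmHg difference.

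**Step 4. Effect of varying the block size.** About 80,000 allocations were simulated for a guesser who sees the whole sequence and knows the set of sizes but not each block's size.

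| Block sizes | Certain | Best guess right |
|---|---|---|
| Fixed 4 | 33% | 70.8% |
| Random 4/6 | 5.4% | 69.3% |
| Random 2/4/6 | 4.3% | 70.2% |
| Random 4/6/8 | 2.1% | 68.1% |

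As a check on the last row, always guessing the arm with fewer assignments so far gives (2.833 + 4.1 + 5.329)/18 = 68.1%.

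**The case against.** A reader might infer that the recruiting physician sees every earlier assignment, so that one allocation in three is simply known. The article does not support that. Each site has its own physician, and nothing says that assignments are shared between sites. One third requires separate card series per community, or pooling, and neither is stated. If the sequence is shared, the certain share is about 2–4%. This part of the objection stands, and one third is an upper bound.

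A reader might also infer that the lack of stratification by community is a defect in itself. The article is silent on whether card series are per community, and a condensed article may leave that to the full protocol. It is a question to answer, not an error.

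The remedy is modest. Varying the block size nearly removes certainty but barely reduces best-guess success. Moving to per-community sequences could make things worse: if the series is now shared, best-guess success would rise from 55–57% to about 68% even with varied sizes.

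Timing also matters. Under Trial status, recruitment began on 10 March 2021 and the trial was expected to finish in June 2022; the article appeared on 16 February 2022. If that finish includes the six months of treatment, enrolment had to end around December 2021, before the block size was published, and nobody remains to be allocated. The article does not say that recruiters were told the block size, that the physician holds the cards, or that cards are opened too early.

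What the objection leaves standing is the combination of one small fixed block, open treatment, and a recruiter who learns the assignments at the own site.

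**Conclusion.** The point holds in limited form. A fixed block of four, with an unblinded physician who recruits and also learns the assignments, does not fully secure the stated lack of prior knowledge. Certain allocations run from about 2–4% to one third, and best-guess success from about 55–57% to 70.8%, depending on a card-series structure that the article does not describe. The figures assume that the recruiter knows or infers the block size and tracks position; the lower ones also assume equal sites and random arrival order.

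Nothing in the article shows that anyone has predicted or steered an allocation, so the mmHg figures are illustrations only. The change is worth making if patients remain to be randomised; otherwise it is a matter of reporting.

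**What to change.** For any randomised patients still to be allocated:

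- Have the independent investigator generate the remaining sequence with randomly varying block sizes, for example 4, 6 and 8, not disclosed to the sites.
- Keep the present sequence structure, whether shared or per community, and state which it is.
- Scratch each card only after consent, eligibility and all baseline measurements are recorded against its number. This matters as much as the block sizes, because best-guess success stays near 68–70% when the whole sequence is visible.

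The cost is a new set of cards from the same independent investigator and a short amendment. The downside is a slightly larger chance imbalance from incomplete blocks.

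If allocation is already complete, report the fixed block size, and whether card series were per community, as a limitation on concealment.

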## Methods/design

### Study design

The study protocol has been registered at ClinicalTrials.gov (Identifiers: NCT04788563), a registry including all items from the WHO Trial Registration Data Set. We developed this article following the Standard Protocol Items: Recommendations for Interventional Trials (SPIRIT) guidelines [16].

This study will be a multicenter, pragmatic, parallel-group, superiority RCT with patient-preference arms. We will recruit patients from seven communities (Wuliangdian, Nangang, Jinsheng, Shajing, Hongmiao, Jinghexinggong, and Erliuling) to which the Affiliated Hospital of Jiangxi University of Chinese Medicine provides primary healthcare services. These communities will first be randomized into a compulsory randomization cluster and a patient preference cluster. For the former, a completely random grouping scheme to the moxibustion group (HSM + their original antihypertensive regimen) or the control group (their original antihypertensive regimen alone) will be used for individual patients; in the latter, patients can directly enter the moxibustion or control group based on their preference for managing hypertension, whereas the patients will be randomized if they have no clear preference. This grouping method will result in four randomized arms and two nonrandomized arms (Fig. 1).

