### Recruitment and compliance enhancement

Patients will be invited to participate in the study by their primary care physician at each site. The recruitment advertisement will also be disseminated through posters and the internet. A full understanding of the 6-month follow-up schedule and signing of the informed consent form are prerequisites for participation. Patients’ long-term trust in their physicians is an essential guarantee of their willingness to participate in the study and comply with the protocol. At each visit, patients will obtain a comprehensive health assessment and recommendations for adjusting their medications for hypertension and other diseases. We will also provide a number of rooms with air conditioning and fume extractors at each study site for the patients to administer HSM.

To promote recruitment and compliance, we will provide the patients in both the randomized and nonrandomized HSM groups with two boxes of moxa rolls (108 rolls) per month, which is enough for consumption during the month. At the baseline visit, we will also give the patients two free moxibustion jars, each equipped with a fleece bag that can be slipped over the outside to prevent burns. At the follow-up visits, we will ask the patients to bring the moxibustion jars with them to determine whether the reported frequency of HSM matches the thickness of soot accumulation on the jars. If a moxibustion jar breaks, we will replace it with a new jar. Patients randomized into the control group will receive two more boxes of moxa rolls and two more moxibustion jars than those in the HSM group after completing the study. Because they are not interested in performing HSM, after completing the study, the patients who voluntarily enter the control group will be given a blood pressure monitor that is of equal value to the moxibustion materials.

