### Sample size estimation

The primary purpose of sample size estimation is to meet the need for statistical power for primary outcome comparison between randomized groups. Based on the results of our previous nonrandomized studies (not yet published) and expert opinion, we assume that the SBP in the HSM group will be on average 5 mmHg lower than that in the control group after 6 months of HSM treatment, with a common standard deviation of 8 mmHg between the groups. With a type I error probability “α” of 0.05 and type II error probability “β” of 0.20 and the allowance of a 20% attrition rate, a minimum of 51 patients in either the randomized HSM or control group is needed, as calculated by the following formula for the superiority design [22]:
$$ N=2\times {\left(\frac{Z_{1-\frac{\alpha }{2}}+{Z}_{1-\beta }}{\upmu_1-{\upmu}_2}\right)}^2\times {s}^2 $$

We ultimately decided to enlarge the total sample size to 400, as a sample of this size can be supported by funding. We administered a small preference survey to 100 patients at the study sites, which showed that the ratio of patients with a preference (a strong willingness to enter the HSM or control group) to those without a preference (accept the randomization) was approximately 6:1. Considering the feasibility of the study and the need for confounder adjustment, we established a sample size for the voluntary randomization group of 40 (20 per group) such that the size of the preference selection (nonrandomized) group would be 240 (120 per group). The remaining 120 patients will be entered into the compulsory randomization group (60 per group). Figure 1 illustrates the sample size scheme for each arm.

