### Statistical analysis

Data analysis of the primary outcome will be based on the full analysis set constructed by the intention-to-treat principle, whereby patients will remain in their original group regardless of contamination. The per-protocol set will also be analyzed by sensitivity analysis for the primary outcome to evaluate whether contamination impacts the direction of the effect. The secondary outcomes will also be compared based on the per-protocol set. The need to impute missing values will be determined by the proportion of and reasons for missing data. If imputation is necessary, appropriate methods, such as the last observation carried forward, “best-worst-case” scenario and multiple imputation regression modeling, will be chosen according to the distribution of the missing values.

Data analysis will be conducted separately for the randomized and nonrandomized groups, and consistency of effect directions between the two sets of analyses will be evaluated. For the randomized groups, repeated-measures analysis of variance will be employed for the continuous variables measured each month; QoL and symptom scale scores will be compared by *t* tests, and categorical variables will be compared by chi-square tests. These analyses will not be adjusted for covariates unless there are factors that are significantly unbalanced at baseline. For nonrandomized groups, we will utilize repeated-measures ANOVA, linear mixed models, and logistic regression models depending on the data distribution; potential confounders will be adjusted for, including age, body mass index (BMI), baseline SBP, duration of hypertension, type of antihypertensive regimen, diabetes, dyslipidemia, smoking, and alcohol consumption. The between-group difference will be measured by the mean differences for continuous outcomes (i.e., changes in SBP, DBP, dosage of antihypertensive drug, QoL, and hypertensive symptom scores) and the risk ratios (RRs) for binary outcomes (i.e., the response to treatment and incidence of new-onset cardiovascular events).

We are also interested in whether there are different blood pressure lowering effects between HSM regimens with different parameters, which will be explored by the following subgroup analyses with prespecified effect directions based on our clinical experience:

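### Once one preference arm is full, later patients must enter the other, so the later-filling arm can hold patients treated against their stated preference and all of the last enrolees

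*Protocol article*

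**What the plan says.** The Study design section of the protocol article says that in the preference cluster "patients can directly enter the moxibustion or control group based on their preference for managing hypertension", with randomisation for those who have no clear preference. The Allocation section qualifies this: "Patients who have a clear preference may be free to choose to enter the HSM or control group, with an allocation ratio of 1:1". It then draws the consequence that "when either nonrandomized group is full, the remaining patients will have to enter another nonrandomized group". Sample size estimation sets these arms at 120 each, 240 in total.

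The only evidence on preferences is a survey of 100 patients, in which the ratio of those with a preference "to those without a preference (accept the randomization) was approximately 6:1". How the patients with a preference divided between HSM and control is not reported.

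The Statistical analysis section analyses the nonrandomised arms separately, with adjustment for confounders including "age, body mass index (BMI), baseline SBP, duration of hypertension, type of antihypertensive regimen, diabetes, dyslipidemia, smoking, and alcohol consumption", and states that "consistency of effect directions between the two sets of analyses will be evaluated". The Discussion expects preference-cluster patients to adhere better and drop out less, and expects the nonrandomised evidence to have better external validity.

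**The concern.** The cap turns free choice into a quota. Once one arm holds 120 patients, someone who clearly wants that arm is entered in the other one and still counted in the preference sample. That patient was neither randomised nor given the chosen treatment. This sits badly with the Study design section, which describes entry by preference, and with the Discussion, whose adherence and external-validity arguments assume that patients receive what they want.

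There is also a timing effect. After the cap is reached, all further nonrandomised enrolment goes to one arm. Recruitment opened on 10 March 2021 and the trial was expected to finish in June 2022, so it spans seasons, and the Discussion names hot weather as a threat to HSM adherence. The named confounders include neither enrolment date nor stated preference nor whether a patient was redirected.

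At stake is how the nonrandomised comparison can be read. It becomes a blend of chosen treatment and treatment against preference, in unknown proportions, with partly non-concurrent arms. That weakens its use as corroboration.

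**Working it through.** **Plan's own figures.** The arms add up: 120 (compulsory) + 40 (voluntary randomised) + 240 (nonrandomised) = 400, and 240:40 = 6:1, matching the survey. The powered figure also reproduces: 2 × ((1.96 + 0.84)/5)² × 8² = 40.19 with unrounded quantiles, and 40.19/0.8 = 50.2, rounded up to 51 per arm. Nothing below depends on that figure.

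**Inputs.** Cap of 120 per arm and total of 240 (Sample size estimation); redirection rule (Allocation). The share p of preference patients who want the more popular arm is not given, so a range is assumed. Every redirected patient is assumed to join.

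**Formulas.**
- Expected number redirected = 240p − 120; divided by 120 for the share of the later-filling arm.
- Number enrolled after the first arm fills = 240 − 120/p.
- Without the cap, variance relative to 120 versus 120 = [1/(240p) + 1/(240(1 − p))] / (2/120); its square root is the standard error (SE) ratio.

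| Preference split | Redirected | Share of later-filling arm | Enrolled after the cap | Variance ratio without cap | SE ratio |
|---|---|---|---|---|---|
| 50:50 | about 6 | 5% | about 12 | 1.00 | 1.00 |
| 60:40 | 24 | 20% | 40 | 1.04 | 1.02 |
| 70:30 | 48 | 40% | about 69 | 1.19 | 1.09 |
| 80:20 | 72 | 60% | 90 | 1.56 | 1.25 |

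The redirected and after-cap figures in the 50:50 row come from simulation (5,000 enrolment sequences per split), because the formulas give zero there and chance alone causes the overflow. The simulation agreed with the formulas at the other splits. At least one patient was redirected in 95% of sequences at 50:50 and in over 99% at 60:40 or beyond.

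**Timing.** At 60:40, 240 − 40 = 200 patients enrol while both arms are open, so the confounding with time is partial. The simulated gap between arms in mean enrolment position was about 6%, 16%, 29% and 37% of the recruitment sequence at the four splits.

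**Excluding redirected patients is not enough.** Late enrolees who did choose the open arm remain: 40 − 24 = 16 at 60:40, about 69 − 48 = 21 at 70:30, and 90 − 72 = 18 at 80:20. Only a restriction to patients enrolled before the first arm filled makes the arms concurrent.

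**Closing a full arm to that preference.** At 70:30 the popular arm fills after 120/0.7 ≈ 171 patients, and the other arm still needs about 69. If only 30% of later preference patients want it, about 69/0.3 ≈ 229 more must be seen, against 69 under the present rule. At 60:40 it is 40/0.4 = 100 against 40. The single-arm tail gets longer.

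**The case against.** The rule is stated openly, as the consequence of a 1:1 ratio, and Study design is a summary, so this can be called a disclosed choice. That is fair, but disclosure does not remove the effect on what the arms contain.

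Several stronger readings are tempting, and the document does not support them:
- **That both arms are affected and treatment is fully confounded with time.** Only the later-filling arm receives redirected patients, and both arms recruit together until the cap.
- **That the nonrandomised arms cannot corroborate anything.** They are used to check direction of effect, with adjustment. The trial is powered on the randomised groups, and preference effects are examined through compulsory versus voluntary randomisation. The article never defines the nonrandomised estimand as treatment under preferred choice.
- **That the recruitment section contradicts the rule.** It says "Because they are not interested in performing HSM, after completing the study, the patients who voluntarily enter the control group" receive a blood pressure monitor. That is limited to volunteers and makes no claim about redirected controls.
- **That enrolment period is ruled out as a covariate.** The confounder list is introduced as a set of inclusions, not as exhaustive. What stands is that the factor which this rule creates is not named.

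The size is also assumed: at an even split it is small. If redirected patients decline to join, selection replaces the override, although the tail still falls in one arm.

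**Conclusion.** The point holds as a limited flaw in a supportive comparison. As written, the rule places patients in the arm that they did not want and puts the last enrolees in one arm, and nothing else in the article undoes this. The expected number redirected runs from about 6 (5% of the later-filling arm) at an even split to 72 (60%) at 80:20. These figures rest on an assumed preference split and on every redirected patient agreeing to join. The powered randomised comparison is unaffected. What suffers is the interpretation of 240 of 400 patients as a preference sample, and the weight that their agreement with the randomised result can carry.

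**What to change.** Remove the forced-entry rule and the 1:1 requirement, and let the two preference arms take their natural sizes within 240. The analysis is covariate-adjusted and does not need equal arms, and both arms then recruit concurrently throughout. The cost is an SE about 2% wider at 60:40, 9% at 70:30 and 25% at 80:20, so it is not negligible if preferences are very lopsided. Closing a full arm to patients with that preference should not be used instead, because it lengthens the single-arm tail.

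Recruitment began in March 2021, so the rule may already have operated. In that case:
- record stated preference and enrolment date for each preference-cluster patient;
- report redirected patients separately from those who chose their arm;
- add enrolment period to the adjustment set in the Statistical analysis section;
- run a sensitivity analysis limited to patients enrolled before the first arm filled.

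These steps cost a little more analysis and a smaller sample. The restricted analysis would keep 120/p patients: 200 at 60:40, about 171 at 70:30 and 150 at 80:20. The Study design and Allocation sections should be reconciled so that both describe the same rule.
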